#### Allocation concealment

For this purpose, after preparing the allocation sequence, the sequence is annotated on paper and placed in opaque sealed envelopes, which will be numbered consecutively. The questionnaires will be coded in the same manner. A questionnaire with the same code will be completed by the person who receives code 1 intervention. The assignment sequence and its concealment will be performed by someone outside the research team.

#### Blinding

Participants, outcome assessor, and statistical analyzer will be blind to which group a participant was placed. The individual entering the data from the participant questionnaires on demographic information, postpartum depression, female sexual functioning, and female quality of life will be blind to which participant was assigned to the auricular acupressure seed group or the sham control group.

#### Treatment fidelity

One of the researchers (SB) is responsible to perform intervention. She has participated specific course on auriculotherapy and is supervised by acupuncturist (MHA) about how to perform the intervention. Approximately 15% of intervention sessions will be run under supervision of the acupuncturist to ensure that all acupoints are chosen correctly.

#### Data management

One of the researchers (SB) will be responsible for collecting data at each study stage and will assign another individual for the task of data entry into the SPSS software. This process will be performed under supervision of NB and ZA.

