### Role and qualification of practitioners

The research team consists of one specialist in auriculotherapy (TO), two specialists in reproductive health (ZA and NB), and one midwifery postgraduate student. The protocol of intervention was designed based on the literature review and expert opinion of TO who is an expert in auriculotherapy and is a journal editor for several international journals. Other team members have been qualified in this technique before designing present research. Participant screening and care providing will be done by SB, and ZA and NB will monitor her during the first 10 sessions to ensure the fidelity of providing intervention.

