### Study procedure

After obtaining the necessary permissions from the Ethics Committee of Qazvin University of Medical Sciences, registration at the Iranian Clinical Trial Registration Center (IRCT), and obtaining the permission from Qazvin Nursing and Midwifery School, the researcher will attend for recruitment in Qazvin Health Centers. The lactating women of each center will be invited for participation. The process and purpose of the research will be explained to those who meet the inclusion criteria. Also, they will be ensured that their information will be kept confidential and that the questionnaires will be anonymous and coded in accordance with the research ethics. They will enter into the study after signing the written consent form. The researcher will ensure that they can leave the study at any time. After enrolling eligible individuals, a simple block randomization will be used. Participants will be randomly assigned to the intervention and control groups.

The questionnaires will be filled out by the participants before the intervention. Then, the intervention (acupressure) will be performed as mentioned above. Evaluation of sexual function in both the intervention and control groups will be performed using the FSFI questionnaire immediately, 1 and 2 months after the intervention. Figure 3 provides the timeline of recruitment, allocation, and assessment.

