## Discussion

To the best of our knowledge, this study is the first randomized clinical trial investigating the effect of ear acupressure on the sexual function of lactating women. The strength of this study is the randomized design with parallel treatment procedures and a large sample size, but due to the importance of the treatment practitioner knowing whether they are placing an adhesive patch with a *Vaccaria* seed or without one, a true double blind study is not possible. Acupressure has no known side effects, is non-invasive, and is easy to use [20, 21]. Therefore, the therapist and clients can develop a sense of closeness, trust, and confidence [20]. Several studies have shown promising results about the effect of ear acupressure on insomnia [20, 22], menstrual cramps and dysmenorrhea [21, 23, 24], premenstrual pain [25], chemotherapy-induced nausea and vomiting [26], smoking cessation [27], obesity [18], and shortness of breath [28]. In the study of Oakley et al., acupuncture was affective in premenopausal women with sexual function [43]. In line with previous literature, this study would provide insights about the impact of ear acupressure on sexual function in lactating women.

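### The plan claims a blinded outcome assessor, but the only data collector it names is the therapist, who knows which patches hold seeds

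*Protocol article*

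**What the plan says.** Four parts of the protocol article bear on who measures the outcome.

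- **Blinding:** "Participants, outcome assessor, and statistical analyzer will be blind to which group a participant was placed". A further sentence says that the person who enters the questionnaire data is also blind.
- **Role and qualification of practitioners:** "Participant screening and care providing will be done by SB". **Treatment fidelity** gives the same initials for the researcher who "is responsible to perform intervention".
- **Data management:** the same initials again. This researcher "will be responsible for collecting data at each study stage" and assigns someone else to enter the data.
- **Discussion:** the practitioner has to know whether a patch holds a seed, so full double blinding is ruled out. It adds that "the therapist and clients can develop a sense of closeness, trust, and confidence".

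On mode of completion, Study procedure says: "The questionnaires will be filled out by the participants before the intervention". The Participants section likewise has the women complete the baseline FSFI themselves, and the Blinding section refers to all the instruments as participant questionnaires. FSFI is repeated immediately, 1 month and 2 months after the intervention. The Abstract places SQOL-F at baseline and 2 months.

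**The concern.** The blinding claim lists the outcome assessor as a role distinct from participants, analyst and data-entry person. When the named roles are traced, the only person who could fill it is the therapist, who is not blind. This is a conflict between statements that the article makes, not a detail left to a fuller document.

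The primary outcome is an intimate self-report. It is gathered three times after a course of ten sessions in which one person has treated the woman. If that person hands out the form, clarifies items, waits nearby or chases late returns, and does so differently by arm even without intent, the answers or their completeness can differ for reasons other than the seeds. A bias that enters when the answers are given cannot be removed in the analysis. Readers of the eventual report would meanwhile be told that outcome assessment was blind.

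**Working it through.** **Tracing the roles**

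| Task | Person named | Aware of arm? | Section |
|---|---|---|---|
| Screening and care | treating researcher | yes, once treating | Role and qualification of practitioners |
| Placing patches | treating researcher | yes | Treatment fidelity; Discussion |
| Collecting data, every stage | treating researcher | yes | Data management |
| Outcome assessor | nobody named | stated blind | Blinding |
| Data entry | separate person | stated blind | Blinding; Data management |
| Analysis | nobody named | stated blind | Blinding |

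Rows three and four conflict unless the outcome assessor is someone other than the collector, and the article names no such person.

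**Do the other safeguards close the gap?**

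- *Self-completion.* It stops the therapist from scoring. It is stated outright for baseline. For follow-up it rests on the nature of the instruments and the label in the Blinding section. It does not exclude presence, help or selective chasing.
- *Coding.* Under Allocation concealment the questionnaires carry the same codes as the allocation envelopes. That protects identity from outsiders, but it does not hide the arm from the person who treats each woman.
- *Blinded entry and analysis.* Both come after the answers have been given.

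**Size**

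The plan gives no figure to reproduce, and the documents hold nothing from which the bias could be estimated. The following shows only how sensitive the comparison would be to an *assumed* shift *b* in the between-arm FSFI difference when the true effect is zero.

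- SD, from the values under Sample size calculation: √[(3.47² + 3.03²)/2] = √10.611 = 3.257.
- Per arm: 38 randomised. After the plan's 10% loss, 38 × 0.9 = 34.2, taken as 34.
- SE = 3.257 × √(2/n): 0.790 for n = 34 and 0.747 for n = 38.
- Rejection rate at two-sided 0.05: 1 − Φ(1.96 − b/SE) + Φ(−1.96 − b/SE).

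| Assumed b (FSFI points) | n = 34 per arm | n = 38 per arm |
|---|---|---|
| 0 | 5% | 5% |
| 0.25 | 6.2% | 6.3% |
| 0.5 | 9.7% | 10.3% |
| 1.0 | 24.4% | 26.8% |

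For scale, the planning difference is 24.65 − 22.27 = 2.38 points. These rates are for a two-group comparison at one time point, not for the planned repeated measures ANOVA.

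**The case against.** The strongest reply is that collecting is not assessing. The women fill in the forms, so each woman is the effective rater, and she is stated to be blind. Responsibility for data collection, placed under Data management, may mean no more than gathering coded forms. The practitioner's lack of blinding is disclosed and is not claimed otherwise. Both arms get the same sessions from the same therapist apart from the seed, so courtesy answers from blinded women should affect both arms alike.

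Much of this stands. It rules out several stronger readings that a reader might infer:

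- *That the therapist rates the outcome, or that the primary result is biased.* Nothing says that she interviews, explains, scores or reads the answers.
- *That rapport alone biases the comparison.* The Discussion's remark on closeness and trust names no arm. A difference between arms needs cueing, help or follow-up effort that depends on the arm, or a failure of participant blinding, which is a separate matter.
- *That baseline is measured after allocation.* Study procedure mentions assignment before the questionnaires, but this is only paragraph order. The Participants section puts the baseline FSFI after screening and before any intervention, and no section says that the envelope is opened first. The Statistical analysis section specifies no baseline-adjusted model into which such a bias could be carried.
- *That a critical difference measures the problem.* With 34 per arm, 1.997 × 0.790 = 1.58 points reaches p = 0.05 in a *t* test at one time point. That is true whatever causes the difference, so it is no evidence of bias.

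The reply does not rescue the claim itself. The Blinding section lists the assessor separately from participants, so it cannot simply mean the participant. Handing out and retrieving forms is still contact with an unblinded person at the point of measurement.

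**Conclusion.** The point holds as an internal contradiction. The article claims a blinded outcome assessor, while its only named data collector treats the women and knows which patches hold seeds. The route to bias is indirect, because the outcomes are self-reported by women intended to be blind. The size is unknown and could be nil, and the illustrative rates depend wholly on the assumed shift.

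The conclusion rests on two readings: that the shared initials denote one person, and that no further collector exists beyond those named. If a separate blinded person does handle the forms, the text must say so. As it stands, the Blinding and Data management sections cannot both be left unchanged.

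**What to change.** Reconcile the Blinding and Data management sections with text such as:

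> At every assessment the woman completes the FSFI and, where scheduled, the SQOL-F in private and seals them in an envelope bearing only her code. The envelope passes unopened to the blinded data-entry person. The treating researcher does not administer or explain the questionnaires and does not see the answers. Queries go to a person who attended no treatment sessions.

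The last condition needs care. Two supervisors monitor the therapist during the first 10 sessions, and the acupuncturist oversees about 15% of intervention sessions, so none of them can be assumed to be unaware of allocation.

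If this cannot be arranged, withdraw the blinded-assessor claim and describe the outcomes as self-reported by participants intended to be blind and collected by the unblinded therapist.

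As a safeguard that costs nothing, also state that the baseline questionnaires are completed before the allocation envelope is opened.

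The cost is envelopes, one revised paragraph and a contact for queries. The data-entry person is already in the plan, but the query contact may have to be found from outside the supervising team. Design, sample size and analysis do not change.

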#### Ethical and safety issues

The research protocol will be reviewed and approved by the Ethics and Human Research Committee of Qazvin University of Medical Sciences (decree code: IR.QUMS.REC.1398.056). It is registered on the Iranian Clinical Trial Registration Center under decree code of IRCT20190626044028N1. In addition, the following ethical considerations will be considered throughout this research: obtaining written informed consent, the volunteer nature of participation in the study, ability to withdraw from the study at any time, and confidentiality of information even during the publication of findings. All ethical issues related to clinical trials will be considered. Informed consent during recruitment phase will be obtained by SB.

## Discussion

To the best of our knowledge, this study is the first randomized clinical trial investigating the effect of ear acupressure on the sexual function of lactating women. The strength of this study is the randomized design with parallel treatment procedures and a large sample size, but due to the importance of the treatment practitioner knowing whether they are placing an adhesive patch with a *Vaccaria* seed or without one, a true double blind study is not possible. Acupressure has no known side effects, is non-invasive, and is easy to use [20, 21]. Therefore, the therapist and clients can develop a sense of closeness, trust, and confidence [20]. Several studies have shown promising results about the effect of ear acupressure on insomnia [20, 22], menstrual cramps and dysmenorrhea [21, 23, 24], premenstrual pain [25], chemotherapy-induced nausea and vomiting [26], smoking cessation [27], obesity [18], and shortness of breath [28]. In the study of Oakley et al., acupuncture was affective in premenopausal women with sexual function [43]. In line with previous literature, this study would provide insights about the impact of ear acupressure on sexual function in lactating women.

## Data Availability

Analyzed data and materials will be de-identified and published.

## Abbreviations

CONSORT: Consolidated Standards of Reporting Trials
SQOL-F: Sexual Quality of Life-Female
